#### M4. Setting goals and objectives in nutrition and physical activity, and modification of irrational beliefs

This aims to help participants identify the barriers that keep them from following the directions given to change their eating habits and activity, identify the role of thoughts in the choices and actions about food and physical activity, to develop self-knowledge strategies, learn the ABC technique, and learn other little tricks that will help them to eat more efficiently, and understand the importance of lunch and snack meals.

#### M5. Setting goals and objectives in nutrition and physical activity, and strategies for overcoming obstacles (emotional regulation, emotional eating and self-control)

This aims to help participants to identify what emotional eating is and discover how to cope with it, learn strategies to implement self-control in situations where compulsive eating behaviour can be observed, become aware of loss of control and learn the STOP! technique, and learn strategies to cope with situations/emotions that could lead to binge eating, as well as emotional regulation strategies.

#### M6. Strategies for overcoming obstacles and solving problems

Its aim is to give more information about the obstacles and barriers that often appear in the process of lifestyle change, and teach another coping strategy: the problem-solving technique.

#### M7. Intervention in body image difficulties and assertiveness

This is designed to help participants to understand the role of body image, identify concerns with their body image, work toward the development of a positive body image, and learn what assertiveness is and some techniques through which to practice it.

#### M8. Relapse prevention

This aims to summarise all the previous concepts and techniques, strengthen the changes made, set strategies to maintain the changes obtained, and prevent possible relapse.

#### Support during the intervention

This intervention is self-administered. A welcome e-mail will be sent when the participant starts the programme. Automatic e-mails will be sent after each module, encouraging the participant to continue to use the programme. To minimise the potential technological barriers that could hinder participation and adherence to the Internet-based intervention programme, patients will be provided with a contact email to answer technical questions or problems that might arise.

The instructions will recommend working on each module for a week. After each module, participants will receive positive feedback messages from the site. All modules include videos, texts, homework, and daily records. The participants can download the necessary files directly from the site.

Researchers will only contact participants if they stop accessing the modules for more than two weeks after they are posted. In this case, a reminder email will be sent. After three weeks without intervention access, a reminder telephone call will be made in order to ask the participants about any difficulties or doubts related to the use of the online protocol and help them solve any problems. The procedure details are shown in Fig. 1.

**Fig. 1 Fig1:**
[figure not shown]
Study flow

### Instruments

Participants in the SII condition will have four assessments: pre-intervention, post-intervention (3 months), Follow-up 1 (6 months), and Follow-up 2 (12 months). Measurements regarding satisfaction with the treatment will be filled out after each intervention module. Participants in the UCM condition will have two assessments: pre-intervention, post-intervention (3 months). At that time they will be invited to receive the Internet-based intervention. All the UCM participants who accept will be assessed again at 6 months (post-intervention), and Follow-up 1 (9 months) and Follow-up 2 (15 months). All the UCM participants who decided not to participant will be assessed at Follow-up 1 (6 months), and Follow-up 2 (12 months). The variables and assessment times are summarised in Table 1.

**Table 1 Tab1:** Study variables and assessment points

Assessment area	Instrument	Time of assessment
Primary outcomes		
Blood pressure	Omron®	Baseline, post-T and follow-ups
BMI	TANITA	Baseline, post-T and follow-ups
Secondary outcome		
Gender, age	Sociodemographic question.	Baseline
Body fat and mass	TANITA	Baseline, post-T and follow-ups
Quality of life	QLI	Baseline, post-T and follow-ups
Other measures		
Physical activity	IPAQ	Baseline, post-T and follow-ups
Self-efficacy	GSES	Baseline, post-T and follow-ups
Intrinsic motivation	BREQ-2	Baseline, post-T and follow-ups
Treatment expectations	Treatment expectations	Baseline
Treatment satisfaction	Treatment satisfaction	Post-T

Follow-up sessions: Post-treatment, 6 and 12 months follow-ups

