**Method:**

A randomized controlled trial will be conducted with 100 patients recruited from the hypertension unit of a public hospital. Participants will be randomly assigned to one of two conditions: a) SII: a self-administered Internet-based intervention protocol; and b) MUC-medical usual care. The online intervention is an Internet-delivered, multimedia, interactive, self-administered programme, composed of nine modules designed to promote healthy eating habits and increase physical activity. The first five modules will be activated at a rate of one per week, and access for modules 5 to 9 will open every two weeks. Patients will be assessed at four points: before the intervention, after the intervention (3 months), and at 6 and 12 months (follow-up). The outcome variables will include blood pressure, and Body Mass Index, as primary outcome measures, and quality of life and other lifestyle and anthropometrical variables as secondary outcome measures.

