### Recruitment and randomization

Participants will be recruited from the patient database of the hospital’s Hypertension Unit. The physicians in this unit will make a selection of patients who fit the inclusion criteria, then, a letter will be sent to these patients informing them of the study and requesting cooperation. Interested patients will be given an appointment at the hospital, where they will receive more detailed information. If patients agree to participate, they will be asked for their informed consent, and after signing, allocated to one of two groups: a) *Self-administered Internet-based Intervention (SII),* or *Usual Medical Care (UMC)*. Randomization will be performed using *random allocation software*. The programme Epidat 4.1 will be used to generate this sequence. The allocation will be carried out by an independent researcher, who will be unaware of the characteristics of the study. The sequence will be concealed until interventions are assigned. Patients will agree to participate before the random allocation and without knowing to which treatment they will be allocated. Study researchers conducting assessments across the whole study will be blind to participant treatment conditions and will be unaware of the group to which any patient belongs.

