#### For participants in Usual Medical Care (UMC)

Patients will receive an explanation of the study, and how to fill out the questionnaires. Internet-based intervention will be offered to them at the end of the study (three months after its end) if they are interested. Patients will be called by their physicians following the usual care protocol.

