### Ethical issues

This project has been approved by the Ethics Committee for Clinical Research at the Hospital de Sagunto (ref: 002-2014-10) and by the Ministry of Health, Social Services and Equality in the Spanish Government (s/n), as a post-authorisation observational study. All participants will be informed of the study characteristics, and data will be treated with complete confidentiality. The requirements of the Organic Law on Data Protection (Law 15/1999 of December 13) will be followed at all times.

Participants will receive an Informed Consent document to sign before knowing which group they are in, but after receiving a general explanation of the study. Participants will also be informed about the completely voluntary nature of the research. For ethical reasons, patients allocated to the control group will have the opportunity to complete the online programme after the data collection.

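### The protocol gives three conflicting times for offering controls the programme; under the month-3 offer, no randomised comparison is possible at 12 months

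*Protocol article*

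**What the plan says.** The Protocol article states the time of the offer to usual-care patients in three places.

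- Instruments, of controls at the 3-month assessment: "At that time they will be invited to receive the Internet-based intervention".
- Procedure, usual-care subsection: "Internet-based intervention will be offered to them at the end of the study (three months after its end) if they are interested".
- Ethical issues: "patients allocated to the control group will have the opportunity to complete the online programme after the data collection".

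The Instruments section also sets three visit calendars.

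- Internet arm (SII): "pre-intervention, post-intervention (3 months), Follow-up 1 (6 months), and Follow-up 2 (12 months".
- Controls "who accept will be assessed again at 6 months (post-intervention), and Follow-up 1 (9 months) and Follow-up 2 (15 months".
- The remaining controls: "All the UCM participants who decided not to participant will be assessed at Follow-up 1 (6 months), and Follow-up 2 (12 months".

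The abstract makes no distinction by arm: "Patients will be assessed at four points: before the intervention, after the intervention (3 months), and at 6 and 12 months (follow-up". Table 1 schedules blood pressure and BMI, the primary outcomes, at baseline, post-treatment and follow-ups, and its footnote gives the follow-ups as 6 and 12 months. The statistical section specifies one between-arm model, a 2×2 condition-by-time ANOVA on pre and post values. It also mentions multilevel regression without naming time points. The randomisation section says that assessors throughout the study "will be blind to participant treatment conditions and will be unaware of the group to which any patient belongs".

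**The concern.** The time of the offer decides how long the trial has an untreated control arm. If controls can start the programme at month 3, every later between-arm figure means something different from the 3-month one. If they wait until data collection ends, a controlled 12-month result is available. The protocol supports both readings, and its abstract and Table 1 lead the reader to expect the second.

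The 12-month visit is the most exposed. Under the Instruments calendar, the only controls measured then are those who turned the programme down. Acceptance is a choice made after randomisation, and in a lifestyle trial it plausibly tracks motivation, which this protocol itself measures as a potential moderator. A difference between the Internet arm and decliners could not be separated from that selection. The trial is described as ongoing, and once controls have taken the programme the untreated comparison cannot be recovered.

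**Working it through.** **1. Can the three offer times be made to agree?** Instruments puts the offer at month 3 and continues data collection to month 12, or to month 15 for accepters. An offer at month 3 therefore precedes the end of data collection, contrary to Ethical issues, unless data collection there means only the first three months. The usual-care subsection names both the end of the study and a point three months later. If the study ends at month 3, the later point is month 3 + 3 = 6; if it ends at month 12, it is month 12 + 3 = 15. No passage defines either term, so the conflict stands.

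**2. Who is measured when, under Instruments?**

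| Month | SII | Controls who accept | Controls who decline |
|---|---|---|---|
| 0 | yes | yes | yes |
| 3 | yes | yes, untreated | yes, untreated |
| 6 | yes | yes, after the programme | yes, untreated |
| 9 | no | yes | no |
| 12 | yes | no | yes, untreated |
| 15 | no | yes | no |

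- Month 3: both arms complete by design, controls untreated.
- Month 6: every control has a visit, so an as-randomised comparison exists, but of immediate versus delayed offer.
- Month 12: no accepter has a visit, so the control arm as randomised is not observed.

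The visit labels also differ. Follow-up 1 and 2 are months 6 and 12 for SII and decliners, but 9 and 15 for accepters. Pooling by label would mix times since randomisation.

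**3. The plan's own sample size.** Inputs from Sample size: d = 0.64, one-sided alpha 0.05, power 0.80. n per arm = 2(1.645 + 0.842)² / 0.64² = 30.2, rounded up to 31; the exact t-test gives 30.9, also 31. The stated 30 reproduces to within one patient. Allowing for 30% dropout, 30 / 0.70 = 42.9, or 43, so the planned 50 per arm is ample.

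**4. Controls left at month 12.** Assumptions: the 30% dropout, stated for this type of intervention, also applies to controls (50 × 0.70 = 35), and a share *a* accepts. The protocol gives no acceptance rate. Decliners = 35 × (1 − *a*):

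- *a* = 50%: 17.5
- *a* = 70%: 10.5
- *a* = 90%: 3.5

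**5. Dilution at month 6 (illustration).** Further assumptions: accepters gain the full d = 0.64 by month 6, the SII effect is still 0.64, and 35 per arm are analysed. Contrast = 0.64 × (1 − *a*). One-sided power ≈ Φ(d√(35/2) − 1.645).

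| *a* | d at month 6 | Power |
|---|---|---|
| 0% | 0.64 | 0.85 |
| 25% | 0.48 | 0.64 |
| 50% | 0.32 | 0.38 |
| 75% | 0.16 | 0.17 |
| 90% | 0.06 | 0.08 |

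**6. Blinding.** All three groups share month 6, and SII and decliners share month 12. The calendars first diverge at month 9. Only the 9- and 15-month visits are attended by one group alone, the accepting controls.

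**The case against.** The strongest reply is that the plan never specifies a between-arm test after month 3. The ANOVA is pre/post, the stated objective concerns a three-month programme, and Instruments gives controls two assessments before the offer. That contrast keeps its randomised, untreated control under every reading. A delayed offer is also a deliberate choice, made for stated ethical reasons. The abstract is a summary, Table 1 sits beside the text that gives the separate calendars, and the study-flow figure is not available to check. All of this stands, and it means the specified 3-month analysis is sound on this point. It does not remove the conflict over the offer time. Nor does it tell a reader that the 12-month values of the primary outcomes have no randomised comparator.

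Two stronger readings are tempting. One is that randomisation is already lost at month 6. It is not: accepters and decliners are both scheduled then, and analysing them together is diluted but free of selection by acceptance. The other is that separate calendars unmask assessors from month 3 onward. They do not: nothing in the calendar identifies the arm at month 6, and a 12-month visit could belong to either arm.

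**Conclusion.** The point holds. The timing conflict and the missing 12-month visit for accepting controls are read directly from the text and need no assumption. Under the Instruments calendar, untreated randomised control ends at month 3, month 6 compares immediate with delayed offer, and month 12 offers no randomised comparison.

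The sizes are illustrative. About 4 to 18 controls would be seen at month 12 if 50–90% accept and the 30% dropout applies to the control arm. At 50% acceptance the month-6 contrast would halve from 0.64 to 0.32, with one-sided power of about 0.38 instead of 0.85, if accepters gain the full effect and the SII effect persists. A reader might infer that the primary result is compromised; the documents do not support that, because the pre/post ANOVA uses only data from before a month-3 offer.

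**What to change.** Reconcile the abstract, the usual-care procedure, Instruments, Table 1 and Ethical issues to one offer time and one visit calendar. Which offer time to adopt is for the sponsor.

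- **If the offer stays at month 3:** state that the 3-month contrast is the only confirmatory between-arm comparison. Any 6-month between-arm comparison should keep all controls as randomised and be labelled immediate versus delayed offer. Report 12-month SII data as uncontrolled within-arm maintenance. Never split controls by acceptance to form a comparator.
- **If the offer follows data collection:** assess all controls at 3, 6 and 12 months.
- **Blinding:** qualify the whole-study statement for the 9- and 15-month visits only.

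The cost is mainly wording and labelling. In substance, either the trial gives up a controlled 12-month claim, or some controls wait longer for the programme.

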### Primary outcomes

The primary outcomes will be the blood pressure levels (arterial brachial systolic and diastolic pressure, determined by Omron®; in millimetres of mercury) and the BMI (Body Mass Index = kilogrammes/height ^2^(meters).

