### Sample size

The sample size for this project was based on the effect size found in previous studies [23, 33–35]. In previous RCT online interventions [33] a moderate effect size (g = 0.64) was found [23] when evaluating bodyweight. Taking this into account, a conservative effect size of .64 (Cohen’s d = .64) is expected in primary outcome measures. An estimation of the desired sample size was made based on the expected difference in the primary outcome variables, BP, BMI. Based on a power of 0.80 in a one-tailed test and an alpha of 0.05, 30 participants in each condition would be required. Considering the high levels (around 30 %) of dropout observed in this type of intervention [36], we chose to increase the expected sample to 50 participants in each condition. The hospital where the study took place selected a list of possible patients based on the inclusion and exclusion criteria.

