### Statistical data analysis

SPSS v.20 will be used for statistical analysis. Relevant statistical analyses will first be performed to verify proper randomization (independent samples *t* test for equivalence of groups). Intention-to-treat and per-protocol analysis will be used. Descriptive statistics for the variables included (mean and 95% confidence interval for normally distributed quantitative variables; and median and interquartile range for abnormally distributed quantitative variables) will be performed. A series of repeated-measures mixed ANOVAs with planned contrasts (2×2) will be carried out: with intergroup variable (condition - OI × UMC) × intragroup variable (time - pre- and post-) for each dependent variable. More sophisticated multivariate analysis, including multilevel regression, will be used. The effect size of improvement and intention-to-treat (ITT) will be estimated.

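### Three co-equal primary outcomes share one undivided one-tailed 0.05 and one power figure, with no rule linking the three tests

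*Protocol article*

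**What the plan says.** **Primary outcomes.** This section of the protocol article reads "The primary outcomes will be the blood pressure levels (arterial brachial systolic and diastolic pressure" and continues "and the BMI (Body Mass Index". That makes three variables: systolic pressure, diastolic pressure and BMI. The abstract agrees ("The outcome variables will include blood pressure, and Body Mass Index, as primary outcome measures"), as does Table 1. None of these places ranks them.

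**Sample size.** "An estimation of the desired sample size was made based on the expected difference in the primary outcome variables, BP, BMI". A common standardised effect of d = 0.64 "is expected in primary outcome measures". The calculation is then stated once: "Based on a power of 0.80 in a one-tailed test and an alpha of 0.05, 30 participants in each condition would be required". The target is raised to 50 per arm for dropout of about 30%. The only effect size attributed to a source there, g = 0.64, is for bodyweight.

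**Statistical data analysis.** Mixed ANOVAs of condition by time (before and after the intervention) are planned "for each dependent variable". The section gives no significance level, order of testing, adjustment, or statement of which results would count as success.

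**The concern.** A single alpha and a single power describe a single test. Here three tests carry primary status, so the trial's conclusion depends on a rule that combines them. Two rules are natural, and each breaks one of the two stated figures:

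- **Any one of the three suffices.** The chance of at least one false positive exceeds 0.05.
- **All three are required.** Error is controlled, but the chance of success is below the power of any single test.

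A mixed result is plausible with about 35 completers per arm, for example BMI significant and blood pressure not. As written, whether that is success or failure would be decided after the data are seen.

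**Working it through.** **Inputs from the protocol article, Sample size:** d = 0.64 for every primary outcome; one-tailed alpha 0.05; power 0.80; 30 per arm needed; 50 per arm planned; dropout about 30%.

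**Inputs assumed, because the article gives none:** correlation between systolic and diastolic pressure 0.5–0.7; correlation between BMI and each pressure 0.1–0.3. The level of 0.05 per outcome is inferred from the sizing.

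**1. Reproduce the plan's figure.** Normal approximation, per arm:
n = 2 × (1.645 + 0.842)² / 0.64² = 30.2, which rounds up to 31. At 30 per arm the power is 0.798. The stated 30 therefore reproduces, for one outcome tested one-tailed at the full 0.05. A two-sided test would need 39, so the one-tailed basis is the one actually used.

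**2. Completers.** 50 × (1 − 0.30) = 35 per arm. The noncentrality is 0.64 × √(35/2) = 2.677. Power for one outcome is Φ(2.677 − 1.645) = 0.85.

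**3. Any-one rule: chance of at least one false success, no true effect, one-tailed 0.05.**
Independent outcomes: 1 − 0.95³ = 0.143. With correlation, 1 − P(all three statistics below 1.645) from the trivariate normal:

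| SBP–DBP | BMI–BP | Error |
|---|---|---|
| 0.5 | 0.1 | 13.1% |
| 0.6 | 0.2 | 12.6% |
| 0.7 | 0.3 | 12.0% |

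Over a wider grid (SBP–DBP 0 to 0.8, BMI–BP 0 to 0.5) the range is 10.9% to 14.3%.

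**4. All-three rule: power with 35 completers per arm, d = 0.64 for each, one-tailed 0.05.**
P(all three statistics exceed 1.645), each with mean 2.677:

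| SBP–DBP | BMI–BP | Power |
|---|---|---|
| 0.5 | 0.1 | 0.65 |
| 0.6 | 0.2 | 0.67 |
| 0.7 | 0.3 | 0.68 |

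If all 50 per arm completed, the figure would be 0.85 at correlations 0.6 and 0.2, so the shortfall depends on the article's own dropout figure.

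**5. Splitting alpha.** At 0.05/3 = 0.0167 one-tailed, power per outcome with 35 completers is 0.71 (normal) or 0.69 (t-based). Reaching 0.80 would take 44 completers per arm, and 44/0.70 = 63 recruited per arm.

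**The case against.** **Left to the SAP.** Multiplicity rules often sit in an analysis plan, which is not shown here, and declaring several primary outcomes is not wrong in itself. That is fair, and the mere absence of an adjustment would not be a finding. But this article itself fixes three primaries and a sample size on one undivided alpha. A later plan that split alpha or required all three would undercut the stated 0.80. Only a named lead outcome makes the calculation fit, and none is named.

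**Stronger readings that the article does not support:**

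- *A reader might infer that each outcome is stated to be tested at 0.05 and that the trial's error rate simply is 13–14%.* The 0.05 appears only in the sizing, and the error figure holds only under an any-one rule that is nowhere stated. On the one-tailed basis, 14.3% is the value under independence, and most of the range under the assumed correlations lies below 13%.
- *A reader might compute all-three power of 0.50–0.55, or 0.59 per outcome at 0.0167.* Those are two-sided figures. Part of the gap from 0.80 then comes from the change of sidedness: single-outcome power drops from 0.85 to 0.76 on that account alone. With two-sided 0.05 tests, false success in favour of the programme would also be only about 6–7% under the assumed correlations (1 − 0.975³ = 7.3% if independent). One- versus two-sided testing is a separate issue.
- *A reader might take systolic pressure as the natural lead.* Nothing in the article ranks it first.

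**Conclusion.** The point holds in conditional form. The sizing describes one test, while the article gives primary status to three and does not say how they combine. An any-one rule therefore puts false efficacy above the stated 0.05, and an all-three rule puts power below the stated 0.80. The sizes in the working rest on the inferred 0.05 level, the assumed correlations, a true d of 0.64 on every outcome and 35 completers per arm. The direction does not depend on the exact correlations: over the wider grid, any-one error is never less than twice the nominal level. Confidence is high that the rule is missing and the sizing does not fit three primaries, and moderate for the figures. This should be corrected. It does not show that the trial would make a false claim.

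**What to change.** Before unblinding, amend the protocol (or fix in the analysis plan, with a matching change to Sample size) to do one of the following for the 3-month comparison:

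1. **Fixed sequence.** Name one lead primary outcome, list the other two in order, and stop confirmatory claims at the first non-significant result.
2. **Holm across the three**, if no order is preferred.

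Then restate the power for the chosen rule. The sponsor chooses the order. Because the only sourced effect size is for bodyweight, the current sizing most directly supports BMI; leading with a blood pressure outcome would need its own justified effect assumption.

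**Cost.** A fixed sequence led by BMI takes one paragraph and no extra patients, and keeps about 0.85 power for the lead test at 35 completers. Its downside is that outcomes after the first failure lose confirmatory status. Holm starts at 0.0167, so its first step has about 0.69–0.71 power per outcome unless recruitment rises. Under either rule all three outcomes are still estimated and reported.
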